### **2.1 Study Overview**

The study will be conducted in the Matlab Health and Demographic Surveillance System (HDSS) field area of the International Centre for Diarrhoeal Disease Research, Bangladesh (ICDDR,B) to determine the population effectiveness of Rotarix in Bangladeshi children. Villages in both the Maternal and Child Health and Family Planning intervention area (hereafter referred to as the ICDDR,B service area) and the comparator Government service area will be included in this evaluation. We propose to introduce Rotarix into half of the villages of the Matlab HDSS. In villages randomized to receive the vaccine, all eligible children will be offered Rotarix during their first two Expanded Programme on Immunization (EPI) visits, as would routinely be done if Rotarix were included in the Bangladesh EPI schedule. If a child residing in a village assigned to Rotarix vaccine did not receive Rotarix during the first EPI visit, the child may still receive the Rotarix during subsequent EPI visits so long as the vaccine is given within age guidelines as defined by the Rotarix package insert. In villages randomized not to receive Rotarix, children will receive their EPI vaccinations exactly as they would have in the absence of this study. Administration of Rotarix will be conducted by regular EPI staff, but ICDDR,B study staff will be present to document informed consent and collect study-specific information. The Ministry of Health will be an active partner in this evaluation since they will be the agency which may follow up with any subsequent vaccine programme. Vaccination with Rotarix will be

recorded on the infant's immunization card which is normally used by the EPI programme, but also on a separate study-specific data collection form.

Rotarix vaccination started in the government service area villages in September 2008 (although was not fully operational until November 1 of that year) and in the ICDDR,B service area villages on April 1, 2009. The delayed start in the ICDDR,B service area was to allow for completion of follow-up in the RotaTeq individually-randomized trial which was carried out in the 67 villages of the ICDDR,B service area.

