| Modified Intent-to-treat (mITT) populations for total effectiveness     | 
First priority analysis
 
Those included: Infants in the “overall effectiveness-secondary analysis” population who 1) received at least one dose of Rotarix and received OPV1 (exclusive of birthdose) while residing in a Rotarix village between 6 and 20 weeks of age after Apr 1, 2009 (ICDDR,B service area) or after Nov 1, 2008 (Govt service area) or 2) received OPV1 (exclusive of birthdose) while residing in a non-Rotarix village between 6 and 20 weeks of age after Apr 1, 2009 (ICDDR,B service area) or after Nov 1, 2008 (Govt service area).
                                                                                                                                                                                                                                                                                                                                                                                                                                                                                                                                                                                                                                                                                                                                                                                                                                                                         |

|                                                                 |                                                                                                                                                                                                                                                                                                                                                                                                                                                                                                                                                                                                                                                                                                                                                                                                                                                                                                                                  |

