|-----------------------------------------------------------------|----------------------------------------------------------------------------------------------------------------------------------------------------------------------------------------------------------------------------------------------------------------------------------------------------------------------------------------------------------------------------------------------------------------------------------------------------------------------------------------------------------------------------------------------------------------------------------------------------------------------------------------------------------------------------------------------------------------------------------------------------------------------------------------------------------------------------------------------------------------------------------------------------------------------------------|
|                                                                 | 
Follow-up period: Person-time will be counted from the date of OPV1 (exclusive of birth dose) until two years (731 days) of age or March 31, 2011, whichever comes first.
 
Second priority analysis
 
Those included: Infants in the “overall effectiveness-primary analysis” population who 1) received at least one dose of Rotarix while residing in a Rotarix village between 6 and 20 weeks of age after Apr 1, 2009 (ICDDR,B service area) or after Nov 1, 2008 (Govt service area) or 2) resided in a non-Rotarix village between 6 and 20 weeks of age after Apr 1, 2009 (ICDDR,B service area) or Nov 1, 2008 (Govt service area).
 
Follow-up period: Person-time will be counted from 6 weeks of age or age of in-migration until two years (731 days) of age or March 31, 2011, whichever comes first.
                                                     |

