| According-to-Protocol (ATP) populations for total effectiveness | 
First priority analysis
 
Those included: Infants in the “MITT total effectiveness first priority” population who complete both the second dose of Rotarix and OPV2 (exclusive of birthdose) in Rotarix villages and OPV2 (exclusive of birthdose) in non-Rotarix villages.
 
Follow-up period: Person-time will be counted from date of OPV2 (exclusive of birth dose) plus 2 weeks until two years (731 days) of age or March 31, 2011, whichever comes first.
 
Second priority analysis
 
Those included: Infants in the “MITT total effectiveness second priority” population who complete the second dose of Rotarix in Rotarix villages and all those from non-Rotarix villages.
 
Follow-up period: Person-time will be counted from 26 weeks of age until two years (731 days) of age or March 31, 2011, whichever comes first.
 |
| “Direct effectiveness” populations                       |                                                                                                                                                                                                                                                                                                                                                                                                                                                                                                                                                                                                                                                                                                                                                                                                                                                                                                                                  |

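### Second-priority mITT total effectiveness: Rotarix-village infants are selected on a dose given at 6 to 20 weeks, but their person-time starts at 6 weeks, before that dose

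*SAP*

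**What the plan says.** SAP section 3.2 (Analysis Populations) defines two mITT and two ATP populations for total effectiveness.

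- **mITT, second priority.** Drawn from the overall-effectiveness primary population. A Rotarix-village infant must have "received at least one dose of Rotarix while residing in a Rotarix village between 6 and 20 weeks of age". A control infant must have "resided in a non-Rotarix village between 6 and 20 weeks of age". The clock for both is: "Person-time will be counted from 6 weeks of age or age of in-migration until two years (731 days) of age or March 31, 2011".
- **mITT, first priority.** A Rotarix-village infant must have "received at least one dose of Rotarix and received OPV1 (exclusive of birthdose) while residing in a Rotarix village between 6 and 20 weeks"; a control infant needs OPV1. The clock is: "Person-time will be counted from the date of OPV1 (exclusive of birth dose").
- **ATP, first priority.** Rotarix-village infants must complete the second Rotarix dose and OPV2, control infants OPV2. The clock is: "Person-time will be counted from date of OPV2 (exclusive of birth dose) plus 2 weeks".
- **ATP, second priority.** Rotarix-village infants must complete the second dose. The clock is: "Person-time will be counted from 26 weeks of age".

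Section 2.1 allows catch-up. If Rotarix was missed at the first EPI visit, "the child may still receive the Rotarix during subsequent EPI visits so long as the vaccine is given within age guidelines".

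Section 3.5, secondary aim 1, takes as its main analysis the overall primary population, with observation from 12 weeks instead of 6. The mITT population enters only in additional analysis b, defined by reference back to the main analysis. No ATP analysis of total effectiveness is listed there.

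**The concern.** In the second-priority mITT population, membership of the vaccinated group is settled by an event that lies in the infant's future when counting begins. Two things follow.

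First, the weeks between age 6 weeks (or in-migration) and the dose are unvaccinated time, but they and any rotavirus episodes in them are booked to the vaccinated group. Nothing in the SAP removes pre-dose time or cases from the total-effect Poisson models. A time-varying covariate for the first dose is planned only for the second direct-effect Cox model.

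Second, a Rotarix-village infant who dies, leaves or reaches 31 March 2011 before being dosed never enters. The control rule asks for residence, not a dose, so it does not select in the same way.

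At stake is the comparability of the arms in an additional estimate of total effectiveness that will be read beside the main one. The other three populations show that a different clock is possible: two are tied to a vaccination visit in both arms, and one uses a fixed age.

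**Working it through.** The SAP states no figure for pre-dose time, so there is none to reproduce. The size can be bounded from its dates.

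**Inputs from the SAP.** Entry at 42 days of age from 1 November 2008 (Government area) or 1 April 2009 (ICDDR,B area); end at 731 days of age or 31 March 2011; qualifying dose at 6 to 20 weeks; 50% effectiveness, as in section 2.5.1, for illustration.

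**Assumptions.** Births uniform over time and equal in the two areas; no death or out-migration in the follow-up calculation; a common dose delay for all infants. The SAP gives no distribution of age at dose, so a range is shown.

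**Maximum per infant.** 20 − 6 = 14 weeks = 98 days. Full follow-up is 731 − 42 = 689 days, and 98 / 689 = 14.2%.

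**Mean follow-up from 6 weeks.** The entry window is 880 days (Government) or 729 days (ICDDR,B). Averaging the smaller of 689 and the days left to 31 March 2011:
- Government: (689 × 690 / 2 + 191 × 689) / 881 = 369,304 / 881 = 419 days
- ICDDR,B: (689 × 690 / 2 + 40 × 689) / 730 = 265,265 / 730 = 363 days
- Pooled: 634,569 / 1,611 = 394 days

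**Pre-dose share** f = (delay in days × infants reaching the dose) / their total person-days. For 4 weeks: 28 × 1,555 / 633,813 = 6.9%.

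**Apparent effectiveness**, true rate ratio 0.5:
- pre-dose rate equal to the control rate: 1 − [f + 0.5(1 − f)] = 0.5(1 − f)
- pre-dose time event-free: 1 − 0.5(1 − f) = 0.5(1 + f)

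| Dose delay after 6 weeks | f | Pre-dose rate = control rate | Pre-dose time event-free |
|---|---|---|---|
| 2 weeks | 3.5% | 48.3% | 51.7% |
| 4 weeks | 6.9% | 46.6% | 53.4% |
| 8 weeks | 13.3% | 43.4% | 56.6% |
| 14 weeks (every infant at the limit) | 22.2% | 38.9% | 61.1% |

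The first column of results dilutes, the second inflates. A pre-dose episode does not by itself bar vaccination under the SAP, so the event-free column is an extreme. Neither column includes any effect of losing infants from the Rotarix arm before dosing.

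**Against sampling error.** With 268 cases split 89.3 to 178.7 and a design effect of 3.48, SE(log RR) = √[3.48 × (1/89.3 + 1/178.7)] = 0.24. The 95% interval for the rate ratio is exp(−0.693 ± 0.474) = 0.31 to 0.80, or effectiveness of about 20% to 69%.

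**The other populations.** In first-priority mITT the clock precedes the qualifying dose only when the first Rotarix dose came after OPV1. In first-priority ATP it can do so when the second Rotarix dose came after OPV2, for example at a third OPV visit. An infant who took the first Rotarix dose at OPV2 would then contribute time between the two doses. Section 2.1 permits both cases; the SAP gives no frequency for either. Second-priority ATP largely avoids the fault by starting at 26 weeks, although it states no upper age for the second dose.

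**The case against.** **The main analyses are clean.** This stands. The primary overall analysis and the main analysis of secondary aim 1 do not select on a dose. A reader might infer that the trial's headline estimates are biased; the SAP does not support that.

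**The 12-week start may carry over.** Additional analysis b refers back to the main analysis and so may inherit observation from 12 weeks. With a dose at 8 to 10 weeks, no pre-dose time would remain for infants resident at 6 weeks. That is a fair reading, but it contradicts the explicit 6-week start in section 3.2, still leaves up to 8 weeks for an infant dosed at 20 weeks, and does not cure selection on a later dose.

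**The control rule is not unconditional.** The residence wording could mean residence throughout 6 to 20 weeks, which would also remove early leavers and deaths among controls. The text does not settle this. Even so, controls would be selected on a different condition from the Rotarix arm.

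**Direction.** A reader might infer that unvaccinated time flatters the vaccine. The arithmetic does not show that: with pre-dose rates equal to control rates the estimate falls. Nor may one infer doses after 20 weeks in this population, since its rule caps the dose at that age.

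**Size.** A shift of 2 to 3.5 points is small beside an interval of about 20% to 69%. That stands too, but this is a systematic error with a simple remedy in the definition.

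**Conclusion.** The point holds for the second-priority mITT population as written: selection on a dose at 6 to 20 weeks, with person-time from 6 weeks or in-migration, misallocates up to 14 weeks per infant to the vaccinated group and drops infants lost before dosing from that arm. On the stated assumptions, with a delay of 2 to 4 weeks, a true 50% would read between about 47% and 53%. The net direction is open, and the size depends on a distribution of age at dose that the SAP does not give. The fault is confined to an additional analysis of a secondary aim. In first-priority mITT and first-priority ATP it is conditional, touching only infants whose qualifying Rotarix dose followed the matching OPV dose.

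**What to change.** **Second-priority mITT.** Start person-time and case counting in both arms at 20 weeks of age, the end of the qualifying window, for infants still resident and under follow-up at that age. State in section 3.5 which start applies to additional analysis b, so that it no longer conflicts with the 12-week start. Say whether control residence means at any time in the window or throughout it.

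**First-priority mITT and ATP.** Do not count time before the qualifying Rotarix dose. For ATP, for example, start the Rotarix-village clock at the later of OPV2 and the second Rotarix dose, plus 2 weeks, or check the result with a common age landmark in both arms. Moving late completers to the 26-week analysis would not work. First-priority ATP descends from the overall secondary population, which adds infants already aged 6 to 20 weeks on the start date; second-priority ATP descends from the overall primary population, which does not include them.

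**Cost.** A change of SAP wording, and the loss of events and person-time between 6 and 20 weeks (at most 14 weeks per infant) in an additional analysis. The later ATP clock shortens follow-up for some Rotarix-village infants only, which is why the common landmark is useful as a check. A 20-week start does not make the arms fully comparable: never-vaccinated infants are still excluded from Rotarix villages alone, and the report should acknowledge that remaining selection on vaccine receipt.

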#### 3.2 Analysis Populations

##### *Exclusions:*

Except for the Total population, there will be no late exclusions from the analyses based on the study’s inclusion/exclusion criteria for immunization. This is to preserve the effectiveness goals of the study.

In the rest of this SAP, “November 1, 2008” and “April 1, 2009” will be used as shorthand for the dates of first study administration of Rotarix in the government service area and ICDDR,B service area, respectively.

Regardless of the analysis, infants are assigned as their village of residence the village in which they were residing when they turned 6 weeks of age, or when they in-migrated (if they in-migrated at an age greater than 6 weeks).

The following participant populations will be used for analyses:

| “Overall effectiveness” (primary objective) analysis populations |                                                                                                                                                                                                                                                                                                                                                                                                                                                                                                                                                                                                                                                                                                                                                                                                                                                                                                                                                                                                                                                                                                                                                                                                                                                                                                                                                                                                                                                                                                       |

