A detailed, yet “black box” analysis will use a Cox regression model with calendar timeline, with baseline hazard stratified by age at entry: 6wks-6 months, 6 months-1 year, 1yr-2yrs. The first step is to determine, for each village, for each day of the study, the time-varying proportion of infants and young children (6wks to 2 years) who have received at least 1 dose of OPV. Then, for each village, we find the 3 dates corresponding to when the village first achieves the proportions: 0.25, 0.50, 0.75. Thus, at any point in time, we can categorize each village into one of four immunization coverage categories: 0-24%, 25-49%, 50-74%, and 75-99%. There may be some misclassification in that a village may reach 27% one day and drop to 20% a month later, but these variations will be too difficult to track, and should not have much effect.

Crossing these four categories with whether a village is a Rotarix or control village yields 8 time-varying categories, which can be represented by 7 covariates:

$$R_{it}^{0-24}, R_{it}^{25-49}, R_{it}^{50-74}, R_{it}^{75+}, C_{it}^{25-49}, C_{it}^{50-74}, C_{it}^{75+}$$

where  $R$  and  $C$  correspond to Rotarix and control villages, respectively,  $i$  is for the  $i$ th infant, and  $t$  is for the infant's age in days. For example, if a given infant living in a Rotarix village is 87 days old on a given day, and on that day the village has already reached 25% coverage but not yet 50% coverage as defined above, then  $R_{it}^{25-49} = 1$  and the other 7 covariates are coded as 0.

Note the reference category is 0-24% coverage in a control village. In addition, we will track the immunization status of each infant with the variable  $Vac_{it}$  which starts as 0 and becomes 1 upon first OPV. This variable is not of much interest—its coefficient will estimate any protective effect due to selection for vaccination. Crossing this term with village type of residence, denoted by  $X_i$  ( $=1$  for Rotarix,  $0$  for control) yields an interaction term that indicates the individual-level protection afforded by Rotarix. Putting this all together into a specification of the hazard function, we get:

$$\lambda_i(t) = \lambda_0(t) \exp(\beta_1 Vac_{it} + \beta_2 X_i Vac_{it} + \beta_3 R_{it}^{0-24} + \beta_4 R_{it}^{25-49} + \beta_5 R_{it}^{50-74} + \beta_6 R_{it}^{75+} + \beta_7 C_{it}^{25-49} + \beta_8 C_{it}^{50-74} + \beta_9 C_{it}^{75+})$$

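### Both second-priority total-effectiveness sets select the Rotarix arm on vaccination and the control arm on residence alone, so these secondary contrasts are confounded by selection for vaccination, in an unknown direction

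*SAP*

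**What the plan says.** SAP section 3.2 defines four populations for total effectiveness.

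- **mITT, second priority.** A Rotarix-village infant must have "received at least one dose of Rotarix while residing in a Rotarix village between 6 and 20 weeks of age". A control infant need only have "resided in a non-Rotarix village between 6 and 20 weeks of age". The clock: "Person-time will be counted from 6 weeks of age or age of in-migration".
- **ATP, second priority.** From the set above, it takes infants "who complete the second dose of Rotarix in Rotarix villages and all those from non-Rotarix villages". The clock: "Person-time will be counted from 26 weeks of age until two years (731 days) of age or March 31, 2011, whichever comes first".
- **mITT, first priority.** Both arms must have received OPV1 (birth dose not counted) at 6 to 20 weeks, and follow-up starts at OPV1. The Rotarix arm must also have had at least one Rotarix dose.
- **ATP, first priority.** Built on the first-priority mITT set. Rotarix villages need the second Rotarix dose and OPV2; control villages need "OPV2 (exclusive of birthdose) in non-Rotarix villages". Follow-up starts two weeks after OPV2 in both arms.

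Under Secondary Aim 1 in section 3.5, the main total-effectiveness analysis uses the overall-effectiveness primary population with observation from 12 weeks of age. It is a Poisson regression with a village-level Pearson scale and terms for arm and service area. Additional analysis b repeats this in the mITT population without saying which priority is meant. Section 3.5 does not name the ATP sets for total effectiveness.

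**The concern.** In the two second-priority sets, the Rotarix arm contains only infants whose families brought them for vaccination. The control arm contains those families and also the ones who would not have come. Randomisation balanced the villages on both kinds of family; the population rule then removes one kind from one arm.

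If non-attenders differ from attenders in their risk of rotavirus diarrhoea, or in how readily they use the treatment centres where cases are detected, that difference enters the rate ratio as if it were vaccine effect. The 26-week clock in the ATP set does not remove it, because the imbalance lies in who is included and not in when counting starts. The planned Poisson model has no term for it.

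The SAP allows for this mechanism elsewhere. In the Cox model under Secondary Aim 2(c), it says of the individual vaccination term that "its coefficient will estimate any protective effect due to selection for vaccination". The Poisson analyses have no counterpart. At stake is whether a second-priority result that disagrees with the first-priority one can be interpreted.

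**Working it through.** **Inclusion rules side by side (SAP section 3.2)**

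| Set | Rotarix arm | Control arm | Attendance matched? |
|---|---|---|---|
| mITT first | OPV1 and ≥1 Rotarix dose | OPV1 | Yes, apart from OPV1 recipients without Rotarix |
| ATP first | mITT first, plus OPV2 and Rotarix dose 2 | mITT first, plus OPV2 | Yes, apart from OPV2 recipients without Rotarix dose 2 |
| mITT second | ≥1 Rotarix dose | Residence only | No |
| ATP second | Rotarix dose 2 | Everyone in the mITT second control arm | No |

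**Inputs**

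- Effectiveness of 50%: the planning value in section 2.5.
- Coverage: the Primary Aim text in section 3.5 expects over 90%, without saying that this means two-dose completion.
- c, the share of infants who meet (or in control villages would meet) the Rotarix-arm rule: assumed 0.95, 0.90 and 0.80.
- r, the detected rate in the remaining infants relative to those who meet the rule, both without vaccine: assumed 0.5, 1.5 and 2. The SAP gives no value.

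The SAP states no figure for this selection effect, so there is none to reproduce. Its sample size does not depend on it.

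**Formula.** Let attenders have rate λ without vaccine and let VE be the true effectiveness among them. The Rotarix arm then has rate (1 - VE)λ, and the control arm has rate cλ + (1 - c)rλ. So

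apparent VE = 1 - (1 - VE) / (c + (1 - c)r).

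This treats c as the share of person-time and leaves indirect effects aside.

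**Worked case, c = 0.90 and r = 2.** The denominator is 0.90 + 0.10 × 2 = 1.10. An inert vaccine reads 1 - 1/1.10 = 9.1%; a true 50% reads 1 - 0.5/1.10 = 54.5%.

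| c | r | c + (1 - c)r | Apparent VE, true 0% | Apparent VE, true 50% |
|---|---|---|---|---|
| 0.95 | 0.5 | 0.975 | -2.6% | 48.7% |
| 0.95 | 1.5 | 1.025 | +2.4% | 51.2% |
| 0.95 | 2 | 1.050 | +4.8% | 52.4% |
| 0.90 | 0.5 | 0.950 | -5.3% | 47.4% |
| 0.90 | 1.5 | 1.050 | +4.8% | 52.4% |
| 0.90 | 2 | 1.100 | +9.1% | 54.5% |
| 0.80 | 0.5 | 0.900 | -11.1% | 44.4% |
| 0.80 | 1.5 | 1.100 | +9.1% | 54.5% |
| 0.80 | 2 | 1.200 | +16.7% | 58.3% |

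**Residual in the first-priority sets.** Use the same formula, with c replaced by the share of OPV recipients in Rotarix villages who also get the required Rotarix. If that share is 97-99% (assumed), an inert vaccine reads +0.5% to +2.9% for r = 1.5 to 2, and -0.3% to -1.0% for r = 0.67. If every OPV recipient also gets Rotarix, it is zero.

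**The case against.** The strongest reply is that little rests on these sets. The main total-effectiveness analysis conditions on vaccination in neither arm, mITT enters section 3.5 only as an additional analysis, and the first-priority sets already carry the safeguard. That stands, and it limits the point to secondary contrasts. It does not remove it: section 3.2 lists the second-priority sets for use, additional analysis b does not exclude the second-priority mITT set, and Secondary Aim 4 repeats the analyses for further severity definitions.

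Section 3.6 also plans a covariate-adjusted total-effect analysis and a Cox total-effect analysis. These may help, but they are exploratory and do not repair the populations.

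It can also be said that adding OPV conditions would make the second-priority sets copies of the first. They would still differ in cohort and clock, so they would keep a use.

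A reader might infer four stronger things that the document does not support:

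- **That all total-effectiveness populations are unbalanced.** The first-priority ATP set inherits the OPV1 match and adds OPV2 in both arms.
- **That selection inflates the vaccine effect.** With r below 1, for instance if families who vaccinate also use the treatment centres more, the estimate falls. The Cox passage allows for a selection effect; it does not assert one.
- **That package-insert age limits remove late attenders from the Rotarix arm only, in the first-priority ATP set.** Section 2.1 mentions those limits but does not give them, so neither the loss nor its size can be shown.
- **That the clause "Except for the Total population, there will be no late exclusions from the analyses" licenses one-sided exclusions.** The immunization criteria it refers to are not listed in the SAP, so this stays conjecture.

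**Conclusion.** The point holds for the second-priority mITT and second-priority ATP sets only. As written, each compares vaccinees in Rotarix villages with all eligible residents in control villages, and the planned model does not correct the resulting confounding. Its direction is unknown.

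For r from 0.5 to 2, an inert vaccine would show about -3% to +5% at c = 0.95, -5% to +9% at c = 0.90 and -11% to +17% at c = 0.80. A true 50% would read about 49-52%, 47-55% and 44-58%. Both c and r are assumptions. The SAP's expected coverage of over 90% points to the narrower ranges for one dose; it does not settle two-dose completion, on which the ATP set depends.

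The primary analysis and the main total-effectiveness analysis are untouched, and the first-priority sets carry at most a small residual under the stated assumptions. This is a worthwhile correction to secondary analyses, not a threat to the trial's main conclusion.

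**What to change.** Apply the first-priority attendance condition to both arms of the second-priority sets, keeping their own cohorts and clocks:

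- **mITT, second priority:** require OPV1 (birth dose not counted) at 6 to 20 weeks in both arms, with at least one Rotarix dose in that window as the added condition in Rotarix villages.
- **ATP, second priority:** require OPV2 (birth dose not counted) before person-time opens at 26 weeks in both arms, with the Rotarix doses as the added condition in Rotarix villages.

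A residual remains for OPV recipients in Rotarix villages who do not get Rotarix, as in the first-priority sets. Reporting their number by village type would let readers judge it. In section 3.5, additional analysis b should also say which mITT set it uses.

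The cost is a change of SAP wording and the loss of a little control person-time in secondary analyses. The primary analysis and the sample size do not change.
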